### Planned data analysis

All statistical analyses are performed using STATA/IC 10.1 for Windows. Analyses will be done on intention to treat (ITT) basis and also per protocol basis, the latter because ITT analyses might underestimate differences between treatment arms in non-inferiority studies, resulting in a false positive study [25]. Number and reasons for exclusion and dropout are reported to ensure internal validity. Missing data on determinants/covariates will be described using descriptive analyses and missing data mechanisms will be studied. Missing values will be imputed using multiple imputation when meeting the assumption of missing (completely) at random, as imputation will increase precision and possibly reduce bias. Logistic regression models with the indicator variable as outcome and the other variables as covariates will be used to check these assumptions. Multiple imputation using chained equations will then be used to estimate missing values. Descriptive statistics will be provided using mean +/-SD, median (p25-p75) or frequencies/percentages depending on the type distribution of the data.

The primary outcome, cumulative incidence of persistent flare is calculated in both groups. The two proportions are then compared using Fisher exact testing. The cost and quality of life are compared between intervention and usual care group for the induction phase and for the maintenance phase separately. Direct costs and indirect cost will be calculated, as will utility based on EUROQOL-5D-5 L. Thereafter, when the intervention is not a clearly dominated or dominant strategy, a decremental cost effectiveness ratio will be estimated using bootstrapping, expressed as saved costs divided by loss in quality of life.

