We have chosen to operationalise low disease activity state by either a DAS28CRP < 3.2 or judgment of low disease activity by the rheumatologist at two subsequent visits at least 3 month apart. This means also patients with a DAS28 ≥ 3.2, but judged to have a low disease activity by their treating rheumatologist, are eligible for inclusion. This is firstly because several biologic registries show that mean DAS28 in TNF Blocker treated patients in clinical practice is around 3.2 [28]. This means that over 50% of the patients has a DAS28 ≥ 3.2, and even more are not in remission, but that both the patient and rheumatologist judge the disease activity to be low enough not to warrant switch of treatment. Limiting inclusion to only patients with DAS28 < 3.2 or even < 2.6 would therefore limit generalisability to current treatment practices. It might be rebutted that these higher disease activity scores reflect undertreatment and thus result in suboptimalisation. A DAS28 can however be inflated by OA associated joint pain, concomitant fibromyalgia or spuriously elevated ESR. This is also the rationale for use of DAS28CRP instead of DAS28 ESR. Another important consideration is that we treat RA patients for two reasons: firstly to improve current signs and symptoms, and secondly to prevent joint damage. With respect to the first reason, it is important to note that the patient acceptable symptom state of the DAS28, has been found to be around 3.5 to 3.9, clearly higher than the currently advocated treatment aims of 2.6 or 3.2 [29]. For prevention of joint damage it is important to realize that not all patients have high risk of erosive disease and a need for prognosis modification [30]. Therefore, accepting somewhat higher disease activity can be legitimate and is indeed part of clinical practice. Of note, per October 19, 2012, all patients (n = 180) have been enrolled and randomised. Mean DAS28CRP is 2.2, and 8% of patients had a DAS28 > 3.2.

Because we aimed for maximal generalisability, we chose to only exclude patients if they have co morbidity which also requires treatment with anti-TNF and thus prevents dose reduction (e.g. Crohns disease), or when it is to be expected that the outcome cannot be measured (short life expectancy, planned major surgery).

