### Outcome measures

The outcome measures used in this study include disease activity (DAS28CRP based RA Flare criterion, mean and time integrated DAS28CRP), function (HAQ DI), radiological damage (Modified Sharp van der Heijde score, MSvdH), Adverse events (CTC 4.0 criteria), utility (Euroqol 5D 5 L) and costs [33-39].

#### **
*Definition of flare*
**

RA Flare in this study is defined in both treatment arms as a DAS28 increase compared to baseline of more than 1.2 or a DAS28 increase of more than 0.6 with a current DAS28 ≥ 3.2 at two separate timepoints at least 4 weeks apart. This criterion has been validated recently, and has been shown to have the optimal tradeoff between sensitivity and specificity, and the best construct and criterion validity [40]. As it has been shown that flares are frequently temporary and occur and disappear without regimen change, a flare is only considered a flare if it is confirmed after at least 4 weeks [11]. Patients are however not left untreated, and when a flare in disease activity occurs, all bridging therapy including i.a. or im steroids or NSAID can be given and are allowed. Of note, flares are defined with change compared to baseline, not compared to the last visit, to prevent undertreatment in patients with a slight increase in disease in subsequent visits.

When the flare is confirmed after 4 weeks, in both treatment arms patients receive optimal treatment for the flare, for example protocollised reinstallment or dose increase of the TNF blocker or change to another biologic or DMARD. Only patients in whom the flare persist longer than three months (in spite of all treatment intensivation) are classified as having persistent flare, the primary outcome of this study.

#### **
*Secondary outcomes*
**

##### 

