### Randomisation, allocation concealment and blinding

Allocation is stratified for adalimumab and etanercept using stratified block randomization in random sized blocks and a ratio of 2:1. Patients will be randomised by the research physician using a computer-generated randomisation list, which has been transferred to paper sheets and put in sealed envelopes.

This study uses a controlled and randomised, but only partly blinded design, as patients and physicians are not blinded for allocation. Blinding of the assessor performing the joint scores was strived for, and this was done by instructing both patients and the independent joint assessor to first score the DAS28CRP, before assessing medication changes and adverse effects.

Although triple blinding (patients, physicians, researcher) would methodologically be preferable, this is unfeasible because dose reduction in this study is done via increasing the interval instead of decreasing the dosage per injection. The latter would not be sensible, since TNF blockers are given using prefilled injection pens. Blinding of patient and physician is possible when using interval widening, but would be very difficult. The unblinded nature of the study could result in information and attribution bias, as flares in patients in whom the dose is reduced would possible be reported sooner because they would be attributed to the intervention. This bias can however fortunately only lead to overestimation of the drawbacks of a dose reduction strategy, not underestimation, and therefore the higher risk of bias was accepted.

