### Sample size

The null hypothesis in this study is that the intervention is inferior compared to the control arm by more than the non-inferiority margin δ (H0: μ1-μ2 > δ). The alternative hypothesis rejects this null hypothesis (H1: μ1-μ2 ≤ δ), thus proving non-inferiority. The sample size calculation is motivated as follows [42] using the fomula as shown.

$$n_{1}=kn_{2}$$

$$n_{2}=\frac{{\left(Z_{a}+Z_{\beta }\right)}^{2}}{{\left(\epsilon -\delta \right)}^{2}}\left[\frac{p_{1}\left(1-p_{1}\right)}{k}+p_{2}\left(1-p_{2}\right)\right]$$

We estimated that 20% (p_1_ = 0.80) of patients will experience the primary outcome in the usual care arm (persistent flare), with an estimated 15% (p_2_ = 0.85) of patients with this outcome in the intervention arm. Applying one sided testing, an alpha of 0.05 (Z_α_ = 1.64, non-inferiority testing one sided), power 1-beta 0.8 (Z_β_ = 0.84), an inferiority margin of 20% (δ = -0.2), and randomisation ratio of 2:1 intervention versus control (k = 2) resulted in n = 114 and n = 57 for intervention and control arm. Accounting for a 10% drop-out, we choose to include 180 patients in total.

The estimation of proportion of primary outcome in both groups and magnitude of the non-inferiority margin (δ) are motivated as follows. Although clear data are absent, based on the few dose reduction studies that included a control group, and on previously published drug survival curves for adalimumab and etanercept in our population, we estimated that after 18 month in the usual care group 15% of patients would have changed their biologic therapy due to insufficient disease control [12,15,16,28]. We furthermore assumed that 15% of patients in the intervention group can ultimately stop the drug (without persistent flare), resulting in cumulative incidence of 85% flares in the group of patients with partial dose decrease. Of these patients, we estimate that 5% will not respond to reinstallment of the TNF blocker and experience a persistent flare. Thus, we expect a cumulative incidence of persistent flare of 15 + 5 = 20% in the intervention arm.

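### The primary Fisher comparison leaves out the randomisation stratum and baseline DAS28: a valid crude comparison, but a little precision is given up that could be recovered at almost no cost

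*Protocol article*

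**What the plan says.** The primary outcome is the cumulative incidence of persistent flare by 18 months. The Planned data analysis section computes it in each arm and then states: "The two proportions are then compared using Fisher exact testing". It names no covariate, stratum or adjusted estimate for this comparison.

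Two other sections bear on this:

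- The section on randomisation describes the scheme as follows: "Allocation is stratified for adalimumab and etanercept using stratified block randomization in random sized blocks and a ratio of 2:1".
- The Outcome measures section gives the event rule: "RA Flare in this study is defined in both treatment arms as a DAS28 increase compared to baseline of more than 1.2". Its second limb counts a rise above 0.6 when the current DAS28 is 3.2 or higher. The section adds that "flares are defined with change compared to baseline, not compared to the last visit".

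For the enrolled population, the section on patients and eligibility reports: "Mean DAS28CRP is 2.2, and 8% of patients had a DAS28 > 3.2".

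The Sample size section sets the test: "Applying one sided testing, an alpha of 0.05", "power 1-beta 0.8" and "an inferiority margin of 20" percentage points, with 114 intervention and 57 control patients before drop-out.

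**The concern.** A single two-by-two table can carry neither a stratum nor a covariate. The drug was thought important enough to stratify on, but the analysis does not use it. If flare rates differ by drug, a standard error that ignores the stratum is somewhat too large.

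Baseline DAS28 enters the endpoint through its definition. Patients starting at different values need different rises to be counted as flaring, and the value is known for everyone before allocation. Leaving it out forgoes whatever precision it offers. It also leaves any chance difference between arms in the estimate, in a trial with about 60 control patients.

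What is at stake is a slightly higher chance of failing to show non-inferiority when it is true. A false claim of non-inferiority is not made more likely.

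**Working it through.** **1. The plan's own figure.** With the article's formula and its values (1.64, 0.84, a distance of 0.15 between the assumed difference and the margin, and k = 2):

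n2 = (1.64 + 0.84)² / 0.15² × [0.80 × 0.20 / 2 + 0.85 × 0.15] = 56.7, so 57 controls and 114 intervention patients.

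This reproduces the stated size. It needs the 20% flare rate in the intervention arm and 15% in usual care, as in the later paragraph of the Sample size section. An earlier sentence there attaches the labels the other way round. I use 20% (intervention) and 15% (usual care) below.

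**2. Unadjusted power against the margin.** SE = √(0.20 × 0.80 / 114 + 0.15 × 0.85 / 57) = 0.0603. Power = Φ((0.20 − 0.05) / 0.0603 − 1.645) = 80.0%. The planned 180 less the stated 10% drop-out is 162, or 108/54, which gives SE 0.0620 and power 78.1%.

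**3. Effect of adjustment.** I multiply the variance by (1 − R²), where R² is the share of outcome variance explained by TNF blocker and baseline DAS28 together. The documents do not give R², so a range is shown.

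| Assumed R² | Power at 114/57 | Power at 108/54 |
|---|---|---|
| 0 | 80.0% | 78.1% |
| 0.02 | 80.7% | 78.8% |
| 0.05 | 81.7% | 79.9% |
| 0.10 | 83.5% | 81.7% |

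**4. How baseline sets the threshold.** The rise needed is more than 1.2 for a baseline up to 2.0. It is 3.2 minus baseline between 2.0 and 2.6 (1.0 at the mean of 2.2), and more than 0.6 from 2.6 upwards. If baseline is normal (my assumption), SD = (3.2 − 2.2) / 1.405 = 0.71. About 39% of patients then fall in the strictest group and about 29% in the most lenient.

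**5. Plausible R² for baseline DAS28.** I simulated one crossing of that threshold. Assumptions: baseline reliability 0.3 to 0.9, added change with SD 0.5, event rates 15% or 20%. R² was about 0.01 to 0.06 when the shape of the relation was left free. A straight-line term captured less, from 0.0002 to 0.046, because the threshold rule and regression to the mean pull in opposite directions.

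**6. Plausible R² for TNF blocker.** R² = s(1 − s)D² / [p(1 − p)], with p = 0.18, s the share of patients on one drug (0.33 or 0.5) and D the difference in flare rate between drugs. D of 5 to 10 points gives 0.004 to 0.02. D of 20 points gives up to about 0.07.

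**7. Chance imbalance.** At 120/60, one standard error of the baseline difference is 0.71 × √(1/120 + 1/60) = 0.11 DAS28 units. The resulting shift in the risk difference is √R² × √(0.18 × 0.82) × √(1/120 + 1/60):

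- R² = 0.01: 0.1 × 0.384 × 0.158 = 0.6 points.
- R² = 0.05: 0.224 × 0.384 × 0.158 = 1.4 points.

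The unadjusted standard error is about 6 points and the margin is 20.

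**The case against.** The strongest reply is that nothing here is wrong. The sample size comes from an unadjusted two-proportion formula, so the stated power does not rely on adjustment. Under randomisation the crude difference is unbiased, and its standard error already allows for chance imbalance in covariates. Stratified blocks keep the drugs nearly balanced. No section says that flare rates differ by drug, and the Background section suggests that success of dose reduction is similar across the agents. All of this stands.

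It is also fair that the simulation in step 5 models a single threshold crossing, whereas the primary event is a flare lasting more than three months despite intensified treatment. Baseline fixes the threshold by definition. How well it predicts persistence is unknown, and even the direction of its effect is unclear. Adjusted supporting analyses may also sit in a full protocol or analysis plan that is not shown.

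What survives is narrow. The article does name the primary comparison, so this is a stated choice and not an omitted detail. Two variables already in hand would fit the analysis better to the design.

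A reader might infer a much larger gain. A correlation of 0.5 between covariates and outcome (variance cut by 25%) would take power from 80.0% to 89.0%. The documents give no support for that correlation, and it lies far above the range in steps 5 and 6. Even a 5-point gain would need R² of about 0.14.

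**Conclusion.** The concern holds as a modest, avoidable loss of precision. For an assumed combined R² of 2% to 10%, the gain is about 1 to 3.5 points of power: 80.0% to 80.7–83.5% at 114/57, and 78.1% to 78.8–81.7% at 108/54. The upper end is generous, and a straight-line term for baseline DAS28 could add almost nothing. Chance imbalance of one standard error in baseline DAS28 is worth about 0.6 to 1.4 points on the risk difference, under a quarter of its standard error.

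These figures rest on 20% against 15% persistent flare, a normal baseline distribution, the assumed R² and a normal approximation to the margin test.

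A reader might also infer that the unadjusted comparison is biased or inflates the risk of a false non-inferiority claim. The documents do not support that: for the stratum, ignoring it is at worst slightly conservative. That an ordinary Fisher test examines no difference, and not the 20-point margin, is a distinct issue. None of its weight is counted here.

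**What to change.** Make the primary estimate a risk difference in persistent flare, intervention minus usual care, in one of two forms:

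- a Mantel-Haenszel risk difference stratified by TNF blocker; or
- a difference standardised over all randomised patients from a logistic model with arm, TNF blocker and baseline DAS28CRP only, with a robust or bootstrap standard error.

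Set its one-sided 95% upper limit against the 20-point margin, and keep the crude difference as a sensitivity analysis. Choose the form before the outcome data are examined.

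The cost is a change of wording and a few lines of code. No new data, visits or patients are needed. The drawbacks are slightly less simple reporting and, for the model, some added dependence on its form. Only about 33 events are expected (120 × 0.20 + 60 × 0.15), about 9 of them in usual care, so no further covariates should be added. If the model looks fragile with so few events, the Mantel-Haenszel form is the safer choice.

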**Methods/Design:**

This study is a 18-months pragmatic, non-inferiority, cost minimalisation, randomized controlled trial on dose reduction and discontinuation of the subcutaneous tumour necrosis factor (TNF) blockers adalimumab and etanercept in RA patients with low disease activity. 180 RA patients with low disease activity (DAS28 < 3.2 or clinical judgment of the rheumatologist) are randomized 2:1 to either increased spacing and eventually discontinuation after 6 months of the TNF blocker, and usual care. Implementation is done in routine daily care, using treat to target and feedback implementation in both treatment arms. The primary outcome is non-inferiority (NI margin 20%) in cumulative incidence of persistent (> 3 months) RA flare, according to a recently validated DAS28 based flare criterion (DAS28 change > 1.2, or DAS28 increase of 0.6 and current DAS28 ≥ 3.2). Secondary outcomes include mean disease activity, function, radiographic progression, safety and cost effectiveness. Cost per quality adjusted life year (QALY) differences between groups are expressed as a decremental cost effectiveness ratio (DCER), i.e. saved costs divided by (possible) loss in QALY.

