The comparison made in this study is between usual care and an alternative strategy (dose reduction) that aims to preserve, but not improve, disease control, whilst minimising the amount of TNF blocker. Therefore, a non-inferiority design (“can we achieve the same effect with less effort”) instead of the classic superiority RCT design (“can we do better with more effort”) was chosen. Of note, this is an adaptation of the original registered research protocol.

#### **
*Study outcome rationale*
**

As disease control is the domain that should remain non-inferior, an outcome measure of disease control had to be selected as primary outcome. Several options come to mind, each with specific advantages and drawbacks.

A straightforward option would be a comparison of disease activity at study end, like for example mean DAS28 with non-inferiority margin of 0.3 DAS28 points. However, it can be expected that at study end no difference is found between the two strategies because patients are treat-to-target, but that flaring is much more frequent during the study in the dose reduction arm. Comparison of time integrated DAS28 might be therefore a better alternative, with the bonus of lower sample size requirements due to the repeated measurements [18]. However, disease activity AUC values are harder to interpret and less informative for a practising clinician than percentage of patients with a flare. The latter also facilitates the calculation of numbers needed to treat/harm (NNT/NNH), thus making results easier to interpret and communicate to patients and physicians alike.

Another option would therefore be to use cumulative incidence of flares as primary outcome, and this is chosen in the majority of dose reduction and discontinuation studies. However, temporary flares that improve after reinstallment of therapy and without a large impact on overall disease control will inevitably occur more frequent in a dose reduction arm, but are clinically less relevant than persisting flares. We therefore chose to assess non-inferiority with respect to cumulative incidence of persisting flare, which is defined as a flare according to the DAS28 based OMERACT validated flare criterion persisting for at least 3 months (independent of treatment changes).

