An interesting alternative for a primary outcome of non-inferior disease control would be to prove superior cost effectiveness of the alternative strategy. This would require proving that either the alternative strategy does not lead to loss of Quality Adjusted LifeYears (QALY) but saves costs (dominant strategy), or that the ratio of saved costs and loss of QALY is favourable. Of note, instead of the common term incremental cost effectiveness ratio (ICER), this approach results in a decremental cost effectiveness ratio (DCER), that states the amount of costs saved per lost QALY. The use of this kind of analyses as primary research question is however challenging due to several issues, and therefore very infrequently employed [25]. Firstly, due to the bootstrapping methods that are used to calculate the DCER, a formal sample size calculation is not possible. Secondly, quality of life is only moderately correlated with RA disease activity, posing a real chance of false reinsurance when quality of life does not seem to be compromised. Thirdly, although ICERs of under 40.000 euro per gained QALY are widely accepted as cost-effective , no such clear-cut threshold is available for DCERs. Although the symmetry of using also 40.000 as threshold for DCER seems attractive, as these saved cost can be used elsewhere in health care system to get more quality of life improvement than was lost, it seems awkward to provide suboptimal therapy in relatively low cost effectiveness ranges. However, it can be argued that when the situation was reversed, e.g., when usual care would be to attempt dose reduction, the alternative of continuing medication would not be considered cost-effective when data shows an ICER clearly over 40.000. Interpretation of DCER seems therefore coloured by anchoring to either the existing and/or the alternative strategy. Anyway, a high DCER of for example > 100.000 saved per lost QALY would probably meet wide acceptance from a cost effectiveness point of view [25].

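### The joint cost-QALY result is planned only as a bootstrapped ratio, which becomes unstable if the QALY loss is as small as the design hopes

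*Protocol article*

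**What the plan says.** The opening of the Objectives section gives the trial two aims: non-inferior disease control and better cost effectiveness. The last secondary objective is to estimate the decremental cost effectiveness ratio (DCER) for the 9-month induction phase and the 12-month maintenance phase.

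The abstract describes the economic result as "saved costs divided by (possible) loss in QALY", with no condition attached. Planned data analysis is fuller:

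- First, "The cost and quality of life are compared between intervention and usual care group for the induction phase and for the maintenance phase separately".
- After that, "when the intervention is not a clearly dominated or dominant strategy", the rule is that "a decremental cost effectiveness ratio will be estimated using bootstrapping, expressed as saved costs divided by loss in quality of life".

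The section does not define *clearly*. It does not say how replicates with zero or negative QALY loss are treated, and it names no interval method.

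Two statements bear on the likely size of the denominator. Study design rationale says the strategy "aims to preserve, but not improve, disease control". Study outcome rationale says "quality of life is only moderately correlated with RA disease activity". The latter section also lists difficulties with the DCER: no formal sample size, the moderate correlation, and no agreed threshold. An unstable denominator is not among them. It mentions 40.000 euro per QALY as the accepted figure for incremental ratios, and "a high DCER of for example > 100.000 saved per lost QALY" as a value likely to be widely accepted.

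**The concern.** A ratio is a poor summary when its denominator may be zero. If the strategy costs little quality of life, bootstrap replicates fall on both sides of zero QALY loss, with two consequences.

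- **Size.** Replicates close to zero give arbitrarily large ratios of either sign, so the mean, percentiles and spread of the replicates are governed by a few near-zero denominators.
- **Order.** Savings with a QALY gain (the best case) give a negative ratio. Extra costs with a QALY loss (the worst case) also give a negative ratio. Replicates can therefore not be ranked from favourable to unfavourable.

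The dominance condition does not clearly prevent this. When a sizeable minority of replicates shows no QALY loss and the rest show some, dominance is not clear on an ordinary reading, so the ratio would be computed where it is least stable. At stake is the joint statement of savings against QALY loss, with its uncertainty.

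**Working it through.** The article gives no numerical DCER, QALY loss, QALY SD or cost SD, so there is no plan figure to reproduce. Everything below except the sample size and the threshold figures is an assumption.

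**Inputs**
- Patients: 180 randomised 2:1 (Sample size), so 120 intervention and 60 usual care, ignoring dropout.
- QALY SD: assumed 0.10 to 0.25 over 12 months.
- QALY loss: assumed 0.01 to 0.02, with 0.05 and 0.10 for contrast. As a plausibility check, the explanation under Sample size expects 20% persistent flare with dose reduction and 15% with usual care. Multiplying the 5-point excess by an assumed utility decrement of 0.1 to 0.3 for a full year gives 0.05 × 0.1 = 0.005 to 0.05 × 0.3 = 0.015 QALY.

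**Step 1: share of replicates with no QALY loss**

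SE = SD × √(1/120 + 1/60) = SD × 0.158. Share with loss ≤ 0 = Φ(−loss/SE). The last column is the loss at which a 95% interval just excludes zero, 1.96 × SE.

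| SD | SE | loss 0.01 | loss 0.02 | loss 0.05 | loss 0.10 | 1.96 × SE |
|---|---|---|---|---|---|---|
| 0.10 | 0.0158 | 26% | 10% | 0.1% | <0.1% | 0.031 |
| 0.15 | 0.0237 | 34% | 20% | 1.7% | <0.1% | 0.046 |
| 0.20 | 0.0316 | 38% | 26% | 6% | 0.1% | 0.062 |
| 0.25 | 0.0395 | 40% | 31% | 10% | 0.6% | 0.077 |

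For a loss of 0.01 to 0.02 the share is 10% to 40%. If loss and SD both scale with time, the 9-month shares are the same: for example, 0.0075/0.0178 = 0.42, as is 0.01/0.0237.

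**Step 2: what this does to the ratio**

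A nonparametric bootstrap was run on five simulated data sets per scenario, with 5,000 resamples each. Assumptions: QALY SD 0.15, mean saving 6,000 euro, cost SD 4,000 euro per arm, costs and QALYs independent. Ranges are across the five sets, in euro per QALY.

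| QALY loss | Saving/loss | 2.5th percentile | Median | 97.5th percentile |
|---|---|---|---|---|
| 0.01 | 600,000 | −4.3 to −3.0 million | 179,000 to 189,000 | 3.7 to 4.4 million |
| 0.02 | 300,000 | −3.1 to −2.7 million | 182,000 to 188,000 | 2.8 to 3.6 million |
| 0.05 | 120,000 | 51,000 to 55,000 | 116,000 to 118,000 | 581,000 to 705,000 |
| 0.10 | 60,000 | 38,000 to 40,000 | 60,000 | 109,000 to 118,000 |

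At a loss of 0.01 the mean of the replicates ranged from −1.8 to +0.8 million across the five sets. Doubling the loss to 0.02 left the median at about 180,000, although the ratio of the means halves.

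**Step 3: net monetary benefit on the same assumptions**

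Net benefit = saving − threshold × QALY loss. SE = √[(4,000 × 0.158)² + (threshold × 0.0237)²].

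- Threshold 40,000, loss 0.01: 6,000 − 400 = 5,600. SE = √(632² + 949²) = 1,140. The 95% interval is about 3,400 to 7,800; the bootstrap gave about 3,300 to 7,900.
- Threshold 100,000, loss 0.01: 6,000 − 1,000 = 5,000. SE = √(632² + 2,372²) = 2,455. The 95% interval is about 190 to 9,800.

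Both intervals are finite and ordered, and they show how the conclusion weakens as the threshold rises.

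**Step 4: a second set of assumptions**

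With SD 0.20, saving 8,000 (SE 900) and loss 0.02, the 95% range of the ratio is about −3.3 to +3.4 million. Net benefit at 40,000 is 8,000 − 800 = 7,200, with SE √(900² + 1,265²) = 1,552 and interval about 4,200 to 10,200.

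**The case against.** Several objections have force.

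- **No percentile interval is prescribed.** This is correct, and a reader should not infer that the article commits to an invalid interval. The percentiles above only describe the replicates. The weakness lies in the ratio as the sole joint summary, since the replicate mean and median mislead too.
- **Costs and quality of life are compared separately first.** This stands. A reader might infer that the cost-effectiveness question cannot be answered at all, but large savings with little QALY difference would be visible. What is missing is the uncertainty of the two taken together.
- **The dominance condition is a guard.** In part. Saved cost per QALY lost has no meaning when no QALY is lost, so withholding it there is sensible. Removing the condition while still printing the ratio would force a meaningless negative figure. The defects are that *clearly* is undefined and that nothing joint replaces the ratio when it is withheld.
- **The small loss is inferred.** This stands. Preserving disease control is not the same as preserving QALYs. The article expects more temporary flares with dose reduction and allows that quality of life may suffer during induction, so the two phases may differ.
- **No DCER threshold is fixed.** This stands. The 40.000 figure belongs to incremental ratios, the authors are uneasy about applying it symmetrically, and 100.000 is only an example. Neither should be read as a decision limit.
- **Such detail belongs in an analysis plan.** Only partly. How replicates are plotted may be left there, but the choice of the ratio is stated in the article.

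**Conclusion.** The point holds conditionally. If the QALY loss is about 0.01 to 0.02, with SD 0.10 to 0.25 and 120:60 patients, 10% to 40% of replicates show no loss. The ratio's bootstrap distribution then spans millions of euro of either sign and cannot describe the uncertainty of the trade-off. On the same assumed data, net benefit at 40,000 euro per QALY is stable and clearly positive. If the loss is about 0.05 (small SD) to 0.10 QALY, the ratio behaves and the concern falls away. Loss, SD and costs are all assumptions.

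The DCER is a secondary outcome with no decision rule attached. The non-inferiority conclusion on persistent flare and the separate cost and quality-of-life comparisons are unaffected. The gap is limited to the aim of better cost effectiveness, which has no joint measure that stays stable in the scenario the design hopes for.

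**What to change.** For each phase, use the planned bootstrap replicates to report incremental net monetary benefit (saved costs minus threshold × QALY loss) with confidence intervals. Show it over a range of thresholds that includes 40.000 and 100.000 euro per QALY, with the cost-effectiveness plane and acceptability curve. Report these whether or not the strategy looks dominant, alongside the cost and QALY differences already planned.

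Replace the undefined *clearly* with an explicit rule. Give the DCER only as a descriptive figure when the replicates show savings together with a QALY loss clearly above zero, for example when the 95% interval of the QALY loss excludes zero.

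The cost is a change of analysis wording, with no new data and no new resampling. The small downside is that the result is shown against a range of thresholds instead of as one number, because the authors fix no DCER threshold.
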